#### 2.3.1. Body Composition

Body mass will be measured in participants with light clothes and barefoot using an electronic balance and standing height with a clinical stadiometer. Body composition (body fat percentage, muscle mass percentage and BMI) will be measured by three techniques: air displacement plethysmography (BodPod, COSMED, Rome, Italy); electric bioimpedance (InBody770, BIOSPACE, Tokyo, Japan); and anthropometry following the standardized protocols of the International Society for the Advancement of Kinanthropometry (ISAK) [25]. The anthropometric variables to include are the ones of the restricted profile (height, body mass, skinfolds (tricipital, subscapular, bicipital, suprailiac, supraspinal, abdominal, anterior thigh, and medial calf)), girths (relaxed arm, flexed arm, waist, hip, and calf) and skeletal breadths (humerus and femur). The measurements’ margin of error will be <2% for skinfolds and <1% for girths and skeletal breadths. Anthropometric dimensions will be measured twice (thrice when measurements are greater than the margin of error) and recorded as a mean. Researchers are certified as ISAK anthropometrists (Supplementary File 2) and are experienced in handling equipment and procedures. Phase angle (50 kHz) will be obtained from the electric bioimpedance analysis.

#### 2.3.2. Dietary Analysis

Energy intake will be assessed weekly by validated 24-h recalls and a semi-quantitative food frequency questionnaire [26], which allows the quantification of the types and quantities of foods and beverages consumed during the period of interest in the past. Dietary records will be reviewed for missing data by an independent nutritionist and then analyzed for calculation of total calories, proteins, carbohydrates, fat, and micronutrients intake (Diet Analysis Plus, ESHA Research, Salem, OR, USA).

#### 2.3.3. Physical Function

Hand grip strength will be evaluated with a Smedley III handgrip dynamometer (Takei Scientific Instruments Co, Tokyo, Japan), while the seated participant held the dynamometer with the arm on the table, the maximum grip strength of each hand will be obtained twice [27]. A functional fitness test (Senior Fitness Test) will be used to evaluate the functional physical condition [28]. The lower-body strength will be assessed by the *30-s chair stand test*, consisting in getting up and sitting down from a chair during 30 s with arms folded across chest. The upper-body strength will be evaluated by the *30-s arm curl test*, consisting in the number of biceps curls finished in 30 s holding a dumbbell (5 lb for women, 8 lb for men). Lower-body flexibility will be assessed by the *chair sit-and-reach test*, where participants begin in a sitting position with leg extended, then slowly flex the hip joint, reaching the fingers as much as to the tip of the toe. *Back scratch test* will assess upper-body flexibility, where the participants will have one hand reaching over the shoulder and the other one un the middle of the back, the distance between the tips of the extended middle fingers will be assessed independently of the back’s alignment. Agility and dynamic balance will be assessed by the *8-foot up-and-go test*, where participants had to get up of from a chair, walk as fast as possible 2.4 m, turn, and sit down again. Aerobic endurance will be evaluated by the *6-min walk test*, where participants have to walk during 6 min around a 50-yard course.

#### 2.3.4. Blood Lipid Profile

Refrigerated blood samples will be centrifugated at 3000 g for 20 min to obtain the plasma, which will be processed to determine total cholesterol (TC), high-density lipoproteins associated cholesterol (HDL-C), low-density lipoproteins associated cholesterol (LDL-C), and triglycerides (TG) by using standard colorimetric procedures (Spinreact, Girona, Spain) with an auto-biochemistry analyzer Mindray BS200 (MINDRAY, Shenzhen, China).

#### 2.3.5. Mental Health and Cognitive Performance

The Montreal Cognitive Assessment (MoCA) will be used to evaluate cognitive performance [29]. Anxiety symptoms will be measured using the Generalized Anxiety Disorder-7 (GAD-7) questionnaire [30]. To assess depressive symptoms, the Patient Health Questionnaire-9 (PHQ-9) will be used [31]. These instruments will be applied in the baseline evaluation and in each of the weekly visits.

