### 2.2. Interventions

The clinical trial consists of two interventions: (1) supplementation with *S. maxima* (5 g/day) or placebo (5 g/day of a low-calorie saccharine), and (2) an exercise program, during a period of 24 weeks in a randomized, double-blind, counterbalanced, crossover, controlled trial with a 2 × 2 factorial design. Presentation of both supplements will be powder encapsulated in dark capsules of 0.5 g to present the same organoleptic attributes and mask their individual characteristics.

Inclusion in the exercise program intervention will be decided by each participant, who will be randomly assigned to one of the two possible nutritional interventions (*S. maxima* or placebo) categorized into four treatments: an exercise program plus *S. maxima* intake; exercise with placebo administration; *S. maxima* intake without exercise, or placebo supplementation without exercise program (Control). To assess compliance to the supplement intake, a crossover will be conducted for the supplementation interventions.

The first period of treatment will be carried out for 12 weeks, followed by a four-week wash-out period to avoid any possible delayed effect of *S. maxima* in the organism. Finally, a further 12 weeks of treatment for the second intervention groups (Figure 1).

Due to absence of data related to wash-out and treatment periods length, we considered 4 and 12 weeks, respectively, as stated by a systematic review of clinical trials that used spirulina as treatment [22].

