#### 2.2.2. Adherence Assessment

Participants will visit the laboratory weekly to receive new supplements and related information, which will be registered on case report formats. Treatment adherence will be assessed by counting the remaining capsules when the participants return to the laboratory. Participants will be asked to report as soon as an adverse effect occurs to analyze the possibility of suspending supplementation.

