### 2.5. Data Collection

Eligible participants will visit the body composition laboratory at UABC in Tijuana, Mexico, between 7–9 AM. They will assist during 3–5 days before the onset of the trial for pre-intervention tests (electrocardiogram, blood chemistry, and a check-up performed by a certified doctor) and familiarization with the exercise program. The first session will be the beginning of the intervention (Day 0), here, antecubital blood samples will be drawn by an expert clinician into EDTA tubes after overnight fasting, after that, body composition measures will be performed, finally, dietary, psychological, and physical activity questionnaries will be obtained. All procedures will be repeated on days 84, 112, and 196. Standard room temperature and humidity will be checked constantly.

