### 2.6. Statistical Methods

Normality and homoscedasticity of variables will be screened by the Shapiro–Wilk and the Levene tests, for each group. The analysis of statistical differences among treatments and time, univariate repeated measures ANOVA with two within-participants (initial and final values), and four inter-participants (treatments) factors will be used. Moreover, basal and post-treatment values will be contrasted by paired *t*-tests. Delta values will be analyzed by one-way ANOVA and Tukey Post-hoc tests (normal distribution and equal variances) and Kruskal-Wallis H and Dunn’s Post-hoc test (non-parametric distribution and unequal variances), with Bonferroni setting for multiple comparisons. Spearman correlations will be run to evaluate the associations among variables. Eventual gen-diet and gen-exercise interactions concerning anthropometric and metabolic outcomes will be assessed by univariate regression analyses. Statistically significance will be set at a *p*-value of 0.05. All statistical analyses will be completed using IBM SPSS package version 23 (SPSS Inc, IBM Company, Chicago, IL, USA) and STATA software (StataCorp, College Station, TX, USA).

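### The MoCA is scheduled at every weekly visit although the stated analysis uses only initial and final values; the intermediate testing adds possible learning and has no described use

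*Protocol article*

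**What the plan says.** Section 2.3.5 names three instruments, the MoCA for cognitive performance, the GAD-7 for anxiety and the PHQ-9 for depression, and gives one schedule for all three: "These instruments will be applied in the baseline evaluation and in each of the weekly visits". Section 2.2.2 confirms that such visits exist: "Participants will visit the laboratory weekly to receive new supplements and related information".

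Section 2.5 describes Day 0 as blood sampling, then body composition, and "finally, dietary, psychological, and physical activity questionnaries will be obtained". It continues: "All procedures will be repeated on days 84, 112, and 196". It names no psychological instrument and does not mention weekly administration.

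The timeline is in section 2.2: "The first period of treatment will be carried out for 12 weeks, followed by a four-week wash-out period", and then a second 12-week period. The article does not say whether weekly visits continue during the wash-out.

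Section 2.6 specifies a repeated measures ANOVA with "two within-participants (initial and final values") and four treatments between participants, paired t-tests of basal against post-treatment values, and a one-way ANOVA of the deltas. Section 2.3 lists cognitive performance within mental health, as a secondary endpoint.

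**The concern.** The MoCA is a test of performance, so a person who sits it repeatedly can score better through familiarity alone. A weekly schedule maximises that exposure, and the stated analysis makes no use of the scores between the start and end of a period.

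Two things are at stake. First, the paired t-tests within each group have no comparator, so a learning gain and a treatment effect look the same to them. The Conclusions section expects a beneficial impact on mental health among other outcomes, so a practice gain could be taken as confirmation. Second, learning during period 1 could raise the score from which period 2 starts, so that changes in the two periods would not be measured on equal terms.

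There is also a practical problem. Staff working from section 2.5 would give the MoCA four times, and staff working from section 2.3.5 would give it every week.

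**Working it through.** **Step 1: are the schedules compatible?** Section 2.5 gives days 0, 84, 112 and 196. Dividing by 7 gives weeks 0, 12, 16 and 28. All are whole weeks, so every main day is also a weekly visit day. The short schedule is contained in the long one.

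**Step 2: count the administrations.**

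| Reading | Calculation | MoCA administrations | Outside the four main days |
|---|---|---|---|
| Section 2.5 only | days 0, 84, 112, 196 | 4 | 0 |
| Weekly, no visits inside the wash-out | 13 (days 0 to 84) + 13 (days 112 to 196) | 26 | 26 − 4 = 22 |
| Weekly, wash-out included | 196/7 + 1 | 29 | 29 − 4 = 25 |

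The two weekly rows differ by the three interior wash-out weeks (days 91, 98 and 105). Day 112 counts as an administration because it is the baseline of period 2.

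**Step 3: set the count against the analysis.** Each 12-week period has 84/7 + 1 = 13 weekly occasions. Section 2.6 uses two of them, initial and final. That leaves 13 − 2 = 11 per period with no stated analytic role.

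**Step 4: which analyses are exposed?**
- Paired t-tests within a group: the mean change is treatment effect plus practice gain, and the two cannot be separated.
- Deltas, S. maxima versus placebo: the supplement is randomised 1:1 and both arms follow the same test schedule. If mean practice is similar in both, the difference is (effect + practice) − (practice) = effect.
- Period 2 values: these start after the 13 administrations of period 1, so the baseline may be higher.

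**Step 5: how sensitive is the paired test?** The article gives no MoCA standard deviation or practice gain, so this step is illustrative only. Assume a two-sided level of 0.05, an SD of change of 2 points, no treatment effect, and an even split of 52 participants into four groups (52/4 = 13; 26 per treatment when both periods are pooled). With d = gain/SD, the chance of a significant result comes from the noncentral t distribution with n − 1 degrees of freedom and noncentrality d√n.

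| Assumed gain | d | n = 13 | n = 26, same gain in both periods |
|---|---|---|---|
| 0.6 points | 0.3 | 17% | 31% |
| 1 point | 0.5 | 38% | 69% |

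The right-hand column requires the full gain in both periods. If the 1-point gain occurs in period 1 only, 13 of the 26 changes have mean 1 and 13 have mean 0. Simulation then gives about 21% in place of 69%. All these values exceed the nominal 5%, but they vary widely with assumptions that the article does not settle. They also describe a practice gain from any source. They do not measure the difference between weekly and four-visit testing, because four visits also repeat the test.

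**The case against.** A reader might infer that sections 2.3.5 and 2.5 contradict each other. They do not. The main days are a subset of the weekly days, section 2.5 never says that questionnaires are given on those days only, and dietary intake follows the same pattern: section 2.3.2 states "Energy intake will be assessed weekly by validated 24-h recalls and a semi-quantitative food frequency questionnaire", and section 2.5 lists dietary questionnaires again at the main visits. The natural reading is weekly assessment plus main visits. This objection stands; what remains is a frequency that is not stated consistently.

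A reader might also infer that practice would bias the comparison of S. maxima with placebo. With 1:1 randomisation, a crossover and one test schedule for all groups, it should largely cancel there. This also stands. A within-group paired test picks up any time trend in any outcome, so that weakness is not peculiar to the MoCA; weekly testing adds one avoidable source of trend. The cancellation is less secure for exercise against no exercise, since participants choose that factor themselves and the groups may differ in their room to improve.

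The argument does not carry over to the GAD-7 and PHQ-9, which are symptom questionnaires. A claim that a ceiling will hide effects in period 2 also lacks support, because the article gives no expected MoCA level or spread.

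Finally, a fuller plan might use the weekly scores. That cannot be excluded, so the point is limited to the analysis that section 2.6 states, which names initial and final values.

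**Conclusion.** The concern holds in a limited form. Section 2.3.5 schedules a performance test 26 to 29 times per participant, while the stated analysis needs four administrations. The 11 intermediate ones per period have no described use and can produce learning. The planned within-group paired t-tests would read that learning as improvement, and it could raise the period 2 baseline.

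The size of any practice gain cannot be derived from the document, and no figure here shows how much smaller it would be with four visits. The conclusion rests on the MoCA being open to practice and on section 2.6 describing the intended analysis. It concerns one component of a secondary endpoint; the primary body composition outcome is untouched and the randomised supplement comparison is largely protected. The change is worth making because it is cheap and gives up nothing that the stated analysis uses.

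**What to change.** - In sections 2.3.5 and 2.5, state the schedule by instrument, and limit the MoCA to days 0, 84, 112 and 196, with alternate versions across those visits where available.
- In section 2.6, base the cognitive conclusion on the between-supplement comparison of changes with a period term, and not on within-group paired t-tests.
- Leave the GAD-7 and PHQ-9 weekly if wanted, and say so in both sections.

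The cost is a short amendment to three sections and the loss of weekly MoCA scores, which no stated analysis uses. The saving is 22 to 25 MoCA sessions per participant. Some practice effect will remain with four administrations, which is why the period term and the between-supplement comparison are still needed.

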#### 2.3.6. Sleep-Wake Patterns

Recording of daily activity and sleep-wake patterns of the participants will be made from actigraphy of continuous recording [32], with three-dimensional accelerometer technology (Mini Mitter, Philips Respironics Inc., Bend, OR, USA) to increase the sensitivity of the instrument. The monitoring will begin one day before starting the study to validate standard sleep patterns and will end once the last measurement is finished, the study will be complemented with the Pittsburgh Sleep Quality Questionnaire [33].

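### The first-period actigraphy baseline is a single pre-intervention day although participants already attend for 3–5 days before Day 0, so the Day 0 sleep value is noisier than it need be

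*Protocol article*

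**What the plan says.** Section 2.3.6 records sleep continuously ("sleep-wake patterns of the participants will be made from actigraphy of continuous recording"). It fixes the start ("The monitoring will begin one day before starting the study to validate standard sleep patterns") and the end (recording "will end once the last measurement is finished"). A questionnaire is added: "the study will be complemented with the Pittsburgh Sleep Quality Questionnaire".

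Section 2.5 describes the run-in: "They will assist during 3–5 days before the onset of the trial for pre-intervention tests". Those days also serve to familiarise participants with the exercise programme. Day 0 is the start of the intervention, and for the later visits the section says "All procedures will be repeated on days 84, 112, and 196".

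Section 2.3 lists change in sleep-wake patterns among the secondary endpoints. Section 2.6 analyses initial and final values by repeated measures ANOVA and paired t-tests, and adds that "Delta values will be analyzed by one-way ANOVA". Section 2.2 places a four-week wash-out between the two 12-week periods.

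The article does not say how many nights make up the initial or the final sleep value.

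**The concern.** The stated purpose of the day before the start is to establish the participant's usual sleep. A single day has no replication, so it cannot separate usual sleep from one unusual night. The night in question also precedes an early-morning fasting visit.

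Whatever error that night carries passes undiluted into every period 1 change score. Later time points can be averaged over many nights, because the device keeps running.

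Day 0 matters most for the exercise comparison. It is the only sleep baseline before the programme starts: by day 112 the exercisers have trained for a full 12-week period, so wash-out nights cannot stand in for it. Exercise is also chosen by the participant (sections 2.2 and Strengths and Limitations). Sleep may therefore already differ between exercisers and non-exercisers at the start, and one night describes that difference poorly.

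This is not a detail that a later analysis plan could settle, since untreated nights that were never recorded cannot be recovered.

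**Working it through.** **Inputs from the article**
- Pre-intervention recording: one day, taken as one night (2.3.6).
- Pre-trial attendance: 3–5 days (2.5).
- Assessments: Days 0, 84, 112 and 196 (2.5).
- Wash-out: four weeks, 4 × 7 = 28 nights, with recording still running (2.2, 2.3.6).

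**Assumptions not in the article**
- Nights are independent with equal within-person variance, s².
- The start of the study in 2.3.6 means Day 0.
- The final value averages kf nights. The article gives no figure, so kf is varied.

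The plan states no figure for the sleep endpoint, so there is none to reproduce.

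**Step 1. Share of the error due to the baseline.** With kb baseline nights and kf final nights, the night-to-night error variance of the change is s² × (1/kb + 1/kf). The baseline share is (1/kb) / (1/kb + 1/kf), and s² cancels. For kb = 1:

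| Final nights kf | Error variance | Baseline share |
|---|---|---|
| 1 | 1 + 1 = 2.000 s² | 50% |
| 2 | 1 + 1/2 = 1.500 s² | 67% |
| 3 | 1 + 1/3 = 1.333 s² | 75% |
| 7 | 1 + 1/7 = 1.143 s² | 88% |
| 14 | 1 + 1/14 = 1.071 s² | 93% |

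**Step 2. Gain from a longer baseline, final window unchanged.**

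| kf | 1 baseline night | 3 nights | 5 nights |
|---|---|---|---|
| 1 | 2.000 s² | 1.333 s² (−33%) | 1.200 s² (−40%) |
| 7 | 1.143 s² | 0.476 s² (−58%) | 0.343 s² (−70%) |

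**Step 3. Equal windows.** With three nights at both ends, the variance is 1/3 + 1/3 = 0.667 s², against 1.333 s² with one baseline night and three final nights (−50%). With five at both ends it is 0.400 s², against 1.200 s² (−67%).

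**Step 4. Period 2.** Up to 28 recorded nights precede day 112. Seven nights at each end give 2/7 = 0.286 s², shared equally. No single-day limit applies.

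**Step 5. Crossover contrast of the two change scores.** If the other three windows each hold k nights, the error variance is s² × (1 + 3/k), and the single day's share is 1/(1 + 3/k): 40% for k = 2, 50% for k = 3 and 70% for k = 7. For k = 7, the variance falls from 1.429 s² to 1/3 + 3/7 = 0.762 s² with three baseline nights, or to 1/5 + 3/7 = 0.629 s² with five.

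**Step 6. Total variance of the change.** True differences between people in how much their sleep changes also count. Take kf = 7, an assumed single-night intraclass correlation of 0.3 to 0.7, and a true-change variance of 0 to 1.0 times the between-person variance. The one-night baseline then makes up between 88% and 29% of the total variance of the change.

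**The case against.** A reader might infer that most of the error in the sleep change score comes from the one-day baseline. The article does not support that as a general statement.
- The final window is not given. With a one-night final value the share is exactly half.
- The limit applies to the first period only, because recording runs through the wash-out.
- The percentages in steps 1 to 5 concern night-to-night error and not all variation in change (step 6). Positive correlation between neighbouring nights would shrink the gain.

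A comparison of day 84 with day 196 within participants would not use Day 0 at all, although section 2.6 does work from initial values and deltas. The questionnaire is a second sleep measure, but it does not repair the actigraphy baseline.

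The averaging rule may well sit in a fuller document, and its absence from an article is no fault. The start of recording, however, is stated here, and it caps what any averaging rule can use.

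Three practical objections stand and shape the remedy. Averaging every available pre-trial day would give baselines of 3 to 5 days that differ between participants. Some of those nights follow familiarisation exercise. Some devices would be worn by people later excluded on the pre-intervention tests (Table 1). Finally, a more precise baseline would not remove the confounding in a self-selected exercise comparison.

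**Conclusion.** The point holds as a cheap improvement of limited reach. The first-period actigraphy baseline is one day when a longer one is feasible, and this adds avoidable noise to the period 1 sleep changes and to the exercise versus no-exercise change. The single day supplies 50% to 88% of the night-to-night error in the period 1 change for final windows of one to seven nights. Three baseline nights would reduce that error variance by 33% to 58%, and five by 40% to 70%.

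These figures rest on independent nights of equal variance and on recording that starts one day before Day 0. If the sponsor means an earlier start, the text should say so and the point falls away.

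It would go too far to conclude that sleep effects will be hidden: the article gives no effect size or variability for sleep from which a loss of power could be worked out. One secondary endpoint is affected. The primary outcome and the sample size of 52 are not.

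**What to change.** Start actigraphy at the first pre-trial visit. Define the baseline as the mean over a fixed number of nights before Day 0 that is available for everyone, at least three where attendance allows. Flag nights that follow familiarisation exercise, or check whether they differ from the others. Use windows of the same fixed length before days 84, 112 and 196, and state that length.

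The cost is about two to four more wear days per person (3 − 1 to 5 − 1) in roughly 196 days of recording, with no added visit. Devices are tied up slightly longer, and some will be worn by people who are then excluded at screening.
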